**Discussion:**

Initial consideration was given to randomizing the groups, however, for a number of reasons, this was deemed to not be possible. In order to ensure that the sites in the immediate intervention and delayed intervention groups are not different from each other, the sites will be assigned to the intervention groups manually to ensure a distribution of the variables as evenly as possible.

Given that HSFO approached this particular group of health care providers to participate in a program relating to hypertension, this may have heightened their awareness of the issue and affected their management of patients with hypertension. Thus, data will be collected to allow an assessment of previous practice patterns and determine any impact of the Hawthorne Effect.

**Trial registration:**

Clinicaltrials.gov NCT00425828

## Background

### Hypertension: Its Burden of Disease

Hypertension is a major risk factor for cardiovascular morbidity and mortality, which in Canada, is the diagnostic category ranked as the highest for drug expenditures[1]. The economic burden of chronic disease in Ontario accounts for 55% of direct and indirect total health costs in Canada [1]. With the current demographic changes in the province of Ontario due to the aging of the 'Baby Boomer' generation, an unusually large cohort born between 1946 and 1965, provincial health plans are grappling with how to plan for the 'silver tsunami' as this generation become senior citizens over the next 23 years. Hypertension, also referred to as the 'silent killer', is a significant chronic health condition, and is prevalent in over 1 out of 5 adult Canadians [2]. Despite being the number one diagnosis listed for patient visits, a substantial proportion of people remain unaware of their hypertension or have not achieved treatment targets [3]. Data compiled by the Heart and Stroke Foundation of Ontario indicate that consumers do not take hypertension seriously, that physicians are not consistently applying clinical practice guidelines related to diagnosis and treatment targets, that patients are not adhering to prevention and treatment recommendations and that physicians lack time and skill to counsel patients about needed lifestyle modifications. Clinical trials demonstrate the efficacy and safety of blood pressure control and clinical practice recommendations provide guidance to achieve blood pressure targets [4]. However, to achieve the benefits from blood pressure control across the entire population, without expending an ever larger fraction of primary care physician's time to the management of this chronic disease, a new paradigm is required. The goal of the Heart and Stroke Foundation of Ontario's Hypertension Management Initiative is a sustainable chronic disease management model for blood pressure control, to economically realize the public health benefits of achieving blood pressure targets and the attendant reduction of heart attack and stroke.

### The High Blood Pressure AIM at HSFO

In 2004, the Heart and Stroke Foundation of Ontario (HSFO) Board of Directors approved a new strategy for making an impact in the fight against heart disease and stroke. This strategy, which is in addition to its ongoing commitment to research and health promotion, would begin to invest in 'Areas of Investment in Mission' (AIMs) as another way to achieve its mission impact.

One of the major components of the HBP AIM Strategy is the Hypertension Management Initiative (HMI) (see Figure 1). The Hypertension Management Initiative focuses on what is acknowledged to be a critical issue in high blood pressure – improving the management of this chronic health condition by primary care providers (doctors, nurse practitioners, nurses and community pharmacists) and patients. Working with several key partners, including the Ontario College of Family Physicians, the Registered Nurses Association of Ontario, and the Ontario Pharmacists' Association, the HMI implements and evaluates a local systems change educational approach designed to enhance physician, nursing and pharmacist approaches to high blood pressure detection, intervention, and follow up measures. In addition, it is intended to improve communication and collaboration between these healthcare providers thus positively impacting patient self management.

**Figure 1 F1:**
[figure not shown]
**High Blood Pressure Strategy**.

The pilot (alpha) phase, "Primary Care Partnerships for Blood Pressure Reduction", was funded by the Ministry of Health and Long-Term Care, in the Province of Ontario, through the Primary Healthcare Transition Fund (PHCTF) and was completed in July 2006. The alpha phase evaluation revealed a statistically significant increase in screening (BP was measured at 45.7% of visits vs. 27.8% pre-program) and diagnosis of hypertension (11% vs. 4.8% pre-program) as well as a trend towards improved follow up and better control (31% of non-diabetic patients controlled vs. 25% pre-program, 58% of diabetic patients controlled vs. 46% pre-program). However the sample size was small at approximately 296 patients. The second phase, termed, the 'HMI Beta Phase', is fully funded by HSFO. The trial will be managed by the Heart and Stroke Foundation of Ontario using a team of experts. To date, eleven provider sites have been recruited across the province.

### Key Objectives of HMI – Beta Phase

The HMI Beta Phase is designed to improve patient outcomes with respect to the control of blood pressure. There are two key elements to the initiative. Firstly, it is designed to improve provider practices and management of essential hypertension. Secondly, it is designed to improve provider-patient interactions and patient self-management of hypertension.

The HMI Beta Phase will achieve these objectives by incorporating various strategies, including inter-professional education, practice outreach and facilitation, an inter-professional healthcare provider toolkit and a patient toolkit (see Table 1). Together, these tools and interventions are intended to enhance collaboration amongst primary healthcare professionals (physicians, nurses, nurse practitioners and community pharmacists) and between healthcare professionals and patients to enhance patient self management of blood pressure and improve the management and control of hypertension. The HMI beta phase also aims to determine and measure the effectiveness of the tools and improve best practice use of the current Canadian Hypertension Education Program (CHEP) recommendations [5] with a larger sample size of healthcare providers and patients than in the HMI Alpha phase. The HMI beta phase aims to measure the effectiveness of this initiative on a larger sample size by roughly quintupling the number of healthcare providers and patients.

**Table 1 T1:** Aspects of the HMI beta phase

• interactive, inter-professional education workshops, reflective exercises
• practice outreach and support to healthcare providers to support and assist in the integration of the tools and interventions in their practices
• inter-professional, evidence-informed healthcare provider toolkit that incorporates clinical reminders and prompts and practice audit feedback and aids inter-professional communication
• evidence-informed, leading edge patient toolkit that provides information and education and supports patient self-management.

The HMI Beta phase is a three-year initiative, which will end in 2010 to determine the effectiveness of the toolkits and interventions on the management and control of hypertension.

## Methods and design

### Overview of the Evaluation Methodology

#### Evaluation Design

To evaluate this initiative, a prospective delayed intervention design has been selected. See Table 2 for key evaluation indicators. Although all sites ultimately will receive the intervention, six of the sites will be assigned to receive the intervention immediately (these sites will be referred to as "immediate intervention group"), while the remaining five sites will receive the intervention after several months, but will serve as a comparison during this delay period (these sites will be referred to as "delayed intervention group"). Further details regarding assignment to the immediate and delayed intervention groups will be discussed in a later section.

**Table 2 T2:** Key Evaluation Indicators of Interest

**Sustainability of the Hypertension Management Initiative program**
◦ Development and usage of information management systems to improve and standardize high blood pressure patient care and treatment and to improve outcomes
◦ Statement of intention by participating healthcare providers to continue using key tools and learnings from the Hypertension Management Initiative.

**Improved hypertension management practices by healthcare providers participating in the Hypertension Management Initiative**
◦ Improved knowledge regarding best practices in management of patients with high blood pressure/hypertension
◦ Improved consistency with current CHEP recommendations in time elapsed from first high blood pressure reading to hypertension diagnosis
◦ Improved healthcare provider medication prescribing for hypertension patients consistent with current CHEP recommendations
◦ Improved assessment of medication adherence and side effects in high blood pressure/hypertension patient visits
◦ Improved assessment of global cardiovascular disease risk in patients with high blood pressure/hypertension
◦ Improved assessment of high blood pressure/hypertension patients' lifestyle risk factors and readiness to undertake lifestyle modifications
◦ Improved provision of support and advice to motivate high blood pressure/hypertension patients to make lifestyle recommendations
◦ Improved follow-up of high blood pressure/hypertension patients consistent with current CHEP recommendations
◦ Improved quantity and quality of inter-professional collaboration in management of patients with high blood pressure/hypertension.

**Improved control of blood pressure among patients reached**
◦ Reduced blood pressure readings of hypertension patients
◦ Increased proportion of patients with hypertension with blood pressure controlled to target
◦ Improved adherence of hypertension patients to prescribed hypertension medication(s)
◦ Improved adherence of high blood pressure/hypertension patients to their selected lifestyle changes

#### Rationale for the Evaluation Design

The reasoning for this delayed approach is that it helps to minimize the potential for threats to internal validity, which are defined as alternate explanations for outcome results other than the impact of the intervention itself. The inclusion of the delayed group controls for outside influences that may occur over time such as educational materials, new research results relating to hypertension or the release of new clinical practice recommendations.

As shown in the timeline (Table 3), the immediate intervention sites will receive the intervention over a 9 month period between Time 2 and 3, including the workshop and all tools developed, whereas the delayed intervention sites will not begin receiving the intervention until Time 3. Thus, between Time 2 and Time 3, it is hypothesized that healthcare providers in the immediate intervention sites will begin to use the tools developed by HSFO and to optimize their management of hypertensive patients. Healthcare providers in the delayed intervention sites will not have received the intervention and are expected to continue with treatment as usual. It is planned that blood pressure measurements will be conducted at Time 3 for patients in both the immediate intervention (after 9 months of the intervention) and delayed intervention (at their baseline) sites. Since the patients in the immediate intervention sites will have been enrolled nine months earlier, it is expected that their blood pressures in follow up visits will be better controlled (due to improvements in provider hypertension management practices stemming from their participation in the initiative and usage of tools developed) than those of their counterparts in the delayed intervention sites who will be providing their baseline BP reading at Time 3 when they are prepared to start the intervention.

**Table 3 T3:** HMI Beta Phase Evaluation Timeline

	**Time 1**	**Time 2**	**Time 3**	**Time 4**	**Time 5**
**Immediate Intervention**	*Measurement:* • BP readings (sphygmom.) • site characteristics • practice patterns re. HTN management	*Receive intervention*: • workshop • tools enrolment of patients *Measurement*: • baseline BP readings (BpTRU)	(continue to receive site support for intervention) *Measurement*: • follow up visit • BP readings (BpTRU)	(continue to receive site support for intervention) *Measurement:* • follow up visit • BP readings (BpTRU)	*Measurement:* • follow up visit • BP readings (BpTRU) • practice patterns re. HTN management

**Delayed Intervention**	*Measurement*: • BP readings (sphygmom.) • site characteristics • practice patterns re. HTN management	treatment as usual	*receive intervention:* • workshop • tools enrolment of patients *measurement*: • baseline BP readings (BpTRU)	(continue to receive site support for intervention) *Measurement:* • follow up visit • BP readings (BpTRU)	*Measurement:* • follow up visit • BP readings (BpTRU) • practice patterns re. HTN management

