**Methods:**

This study will test the effect of a systems change on the management of high blood pressure in real world practice in primary care in Ontario, Canada. The systems change intervention involves an interprofessional educational program bringing together physicians, nurses and pharmacists with tools for both providers and patients to facilitate blood pressure management. Each of two waves of subjects were enrolled over a 6 month period with the initial enrollment between waves separated by 9 months. Blood pressure will be measured with the BpTru ^® ^automated blood pressure device. To determine the effectiveness of the intervention, a before and after analysis within all subjects will compare blood pressure at baseline to annual measurements for the three year study. To assess whether the intervention has an impact on blood pressure control independent of community trends, a betwen group comparison of baseline blood pressures in the delayed wave will be made with the immediate wave during the same time period, so that the immediate wave has experienced the intervention for at least 9 months. The total enrollment goal is 5,000 subjects. The practice locations include 10 Family Health Teams (FHTs) and 1 Community Health Centre (CHC) and approximately 49 primary care physicians, 15 nurse practitioners, 37 registered nurses and over 150 community pharmacists across the 11 communities throughout the province of Ontario. The 11 primary care sites will be divided into immediate and delayed groups based on geography and the use of an electronic versus a traditional chart patient record.

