#### Patient Recruitment Strategy and Consent

Shortly before attending the Launch Workshop, the healthcare providers will identify potential eligible patients for the HMI Beta Phase, based on identified inclusion and exclusion criteria. Each full time equivalent rostering physician and nurse practitioner is requested to recruit a minimum of 100 patients and up to a maximum of 200 patients. A patient friendly consent form has been developed and will be signed by each participant. Copies of the consent, an accompanying script and other materials will be provided to each participating office. In addition to these documents, an implementation guide will also be provided to each site. (Thorough explanations of the materials will also be provided by Heart and Stroke Outreach and Practice Support Specialists at 'on site' visits.)

Appointments with the potential eligible patients will be scheduled to occur subsequent to the workshop with the participating practitioners. During this visit, these potential eligible patients will be provided with information about the HMI Beta Phase, patient consent will be requested and documented and a baseline assessment including physical measures conducted and documented. When a patient provides consent, (s)he is deemed to have enrolled in the HMI Beta Phase. Ethics approval has been obtained from the Sunnybrook Health Sciences Centre Research Ethics Board (approval #: 474-2006).

Utilizing adult learning best practices, the format of the site initiation Launch Workshop is one in which physicians, pharmacists and nurses will learn together and discuss barriers and solutions to better manage hypertension together and via small group breakout sessions, develop a community practice plan to improve the management and control of hypertension among their patients. The purposes of this interactive, inter-professional workshop include addressing any knowledge gaps identified in the healthcare provider needs assessment, introducing concepts of systems change theory and related applications, and developing approaches to high blood pressure based on inter-professional teamwork. This will be accomplished by providing information/education on best practices in management of hypertension, and a tool kit of supporting practice and behaviour change tools to all participating healthcare providers.

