After patient information is entered into the dataset, monthly and quarterly confidential practice audit reports will be available to all practitioners on the secure website linked to the web-based dataset. Moreover, the practitioner will be able to access the data set at anytime and generate ad hoc "drill-down" reports on his/her patients only. While the same practitioner can compare aggregate data from different sites, he/she cannot access the individual patient information of another physician. The web-based dataset will generate regular confidential practice reports based on the data submitted, for each participating physician and nurse practitioner, comparing the practice to that of other providers at the same site and to those of the other sites and participating healthcare providers. Reports are also generated at a site level for the other healthcare providers to access.

The web-based dataset will be hosted on a Personal Health Information Protection Act (PHIPA) compliant server provided by the dataset developer.

The patient will also be offered the patient toolkit, including the "Take the Pressure Off" patient book. This patient resource provides information and education on hypertension, its risk factors, lifestyle change information, and lists other resources. The Patient-Provider Agreement will be reviewed and completed, including the BP goal, the patient's selected lifestyle risk factor which (s)he wishes to focus on in the coming months/years and the patient's personal plan of action for this selected lifestyle risk factor. The Patient-Provider Agreement is incorporated into the "Take The Pressure Off". The BP goal and patient selected lifestyle risk factor is also documented in the HBP Registration (baseline) and Flow sheet (follow-up) data forms.

In order to assess the impact of the Hypertension Management Initiative on both healthcare provider practice patterns and patient blood pressure readings and control, it is necessary to compare data from the pre-program period to the program period. In order to assess any changes from before to after the intervention, a combination of chart reviews, for the pre-program period, and the web-based patient dataset, for the program period, will be used. Thus, data about the practice patterns of individual healthcare providers and their individual patients' blood pressure data will be used as their own comparators pre-intervention versus post-intervention.

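### The Time 3 comparison sets enrolment-visit readings in the delayed wave against return-visit readings in the immediate wave, so attendance selects the two waves unequally

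*Protocol article*

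**What the plan says.** The Abstract (Methods) defines the between-group test: "a betwen group comparison of baseline blood pressures in the delayed wave will be made with the immediate wave during the same time period". By then immediate-wave exposure to the program is meant to be nine months or more. The stated purpose of the test is to show an effect independent of community trends.

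Rationale for the Evaluation Design plans Time 3 measurements for "patients in both the immediate intervention (after 9 months of the intervention) and delayed intervention (at their baseline) sites". It expects better control in the immediate wave ("it is expected that their blood pressures in follow up visits will be better controlled") and attributes this to improved provider practice and use of the tools.

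Table 3 gives the source of each Time 3 reading. For the immediate sites it is "follow up visit • BP readings (BpTRU"). For the delayed sites it is the baseline BpTRU reading, listed with patient enrolment.

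Patient Recruitment Strategy and Consent places consent and the baseline measurements at the same appointment, and states: "When a patient provides consent, (s)he is deemed to have enrolled in the HMI Beta Phase".

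For the before-after assessment, Implementation of Toolkit and Interventions plans "a combination of chart reviews, for the pre-program period, and the web-based patient dataset, for the program period, will be used". The only adjustment for group differences, under Assignment to Immediate Intervention and Delayed intervention groups, concerns differences present before the program. Statistical Design and Analysis adds two-sample t tests, chi-square tests and regression on covariates known to affect blood pressure.

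**The concern.** An enrolled delayed-wave patient has a Time 3 reading almost by construction, because enrolment and the reading happen at one visit. An enrolled immediate-wave patient has one only after coming back. The immediate wave, as measured, has therefore passed two attendance filters and the delayed wave one.

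If patients who do not return have higher blood pressure than those who do, the immediate wave looks better at Time 3 with no program effect. If well-controlled patients are recalled less often, the error runs against the program. The rationale section presents the delayed design as protection against alternative explanations but does not mention this one. The before-after analysis cannot stand in for the contrast, because it does not separate the program from community trends. At Times 4 and 5 both waves depend on follow-up visits, so the problem is confined to Time 3.

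**Working it through.** **Inputs from the document.** Target difference 5 mmHg, 337 per group, two-sided alpha 0.05 (Statistical Design and Analysis). Enrolment goal 5,000 (Abstract). Alpha-phase control 31% vs 25% in non-diabetic and 58% vs 46% in diabetic patients (The High Blood Pressure AIM at HSFO).

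**Inputs that are assumptions.** d, the share of enrolled immediate-wave patients with no Time 3 reading; D, the mean blood pressure of non-returners minus that of returners; and the SD, which is not printed.

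**Reproducing 337.** n = 2 × SD² × (1.960 + 1.282)² / 5². With SD 20 and power 0.90 this is 2 × 400 × 10.51 / 25 = 336.2, so 337. The document also states beta = 0.20, which does not agree with power 0.9. At power 0.80 an SD of about 23.2 would be needed (338). SD 20 is used below.

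**Shift in mean blood pressure.** The mean of all enrolled is (1 − d) × returners + d × non-returners, so the returners' mean lies below it by d × D.

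- 0.10 × 4 = 0.4 mmHg (8% of 5)
- 0.20 × 5 = 1.0 mmHg (20%)
- 0.20 × 10 = 2.0 mmHg (40%)
- 0.30 × 10 = 3.0 mmHg (60%)

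With D = 0 the shift is zero. With D negative the same sizes count against the program.

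**Allowing for the delayed wave.** Let e be the share of comparable delayed-site patients who fell away before Time 3 without being replaced by similar patients, and E their gap. The net shift is then d × D − e × E. If D and E have the same sign, d × D is an upper value. It is reached when e × E = 0 and cancels when e × E = d × D. Full cancellation is not assured: the delayed sample still includes patients who attend the enrolment visit and will not return, and the measured immediate sample has lost its counterparts.

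**Effect on the 5% error rate with no true effect.** SE = 20 × √(1/[n(1 − d)] + 1/n), taking the full shift d × D and no clustering by site. The 2,500 per wave is assumed, as half of 5,000.

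| d | D (mmHg) | shift (mmHg) | 337 per group | 2,500 per wave |
|---|---|---|---|---|
| 10% | 5 | 0.5 | 0.062 | 0.138 |
| 20% | 5 | 1.0 | 0.094 | 0.385 |
| 20% | 10 | 2.0 | 0.232 | 0.915 |
| 30% | 10 | 3.0 | 0.424 | 0.998 |

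For the second row at 2,500: SE = 20 × √(1/2,000 + 1/2,500) = 0.60 and 1.0/0.60 = 1.67, giving 0.385. A larger sample makes a fixed shift more likely to be declared significant. Enrolling 422 instead of 337 to allow for 20% loss restores precision and leaves the shift unchanged.

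**Control proportion.** Assume 20% missing, control 15 points lower in the missing, and 31% in all enrolled: 0.8x + 0.2(x − 0.15) = 0.31, so x = 0.34. The excess is 3 points. That is half the alpha-phase change in non-diabetic patients (31 − 25 = 6) and a quarter of that in diabetic patients (58 − 46 = 12).

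**The case against.** - **The delayed wave is also selected on attendance.** Its candidates are identified shortly before the Launch Workshop and must then attend and consent. Someone who left a delayed site in the preceding nine months is unlikely to be enrolled. This stands. A reader might infer that dropout touches one arm only; the recruitment section does not support that. What remains is unequal selection, with d × D as an upper value.
- **The analysis set is not spelled out.** No sentence says that only returners are counted. That is inferred from Table 3, and the article speaks of planned Time 3 measurements in both groups. This also stands, and an unseen analysis plan may contain a missing-data method. But the article itself fixes an enrolment reading against a follow-up-visit reading, and the adjustments it describes do not address selective return.
- **Data capture is easier than it may look.** A reader might suppose that every immediate-wave reading depends on a flow sheet being sent. Electronic-record sites export nightly, and Table 5 lists six of the 11 sites as electronic. Faxing or manual entry is a hurdle only at paper sites. Everywhere, though, a reading still requires a visit.
- **Size and direction are assumed.** This is correct. The document gives neither retention nor a returner/non-returner difference.

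**Conclusion.** The concern holds as one of unequal selection by attendance in the Time 3 contrast. The two waves' readings come from different kinds of visit, and nothing described in the article corrects for selective return. If return is related to blood pressure, the contrast is biased; if it is not, there is no bias from this source.

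Under the assumed 10-30% non-return and 4-10 mmHg gap, the shift is 0.4-3.0 mmHg against the 5 mmHg target. This is an approximate upper range, because offsetting loss at the delayed sites would shrink it. The error rates rest further on SD 20, the assumed wave sizes and no clustering.

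A reader might infer that the bias flatters the program. The document does not support a direction: less adherent patients may be the ones who fail to return, or well-controlled patients may be recalled less often.

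**What to change.** For the Time 3 contrast:

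- Define the immediate group as all enrolled immediate-wave patients. Each wave is then defined by one attended enrolment appointment.
- Estimate the immediate wave's Time 3 mean blood pressure and control proportion with a likelihood-based longitudinal model, or inverse-probability weighting, that uses the enrolment BpTRU reading and all later readings.
- Show the returners-only comparison beside it.
- Report by site the share of immediate-wave patients with a Time 3 reading, and the enrolment blood pressure of returners against non-returners.
- Do not count patients without a reading as not controlled in the main contrast. That penalises only the immediate wave, since delayed-site non-attenders are never enrolled.
- Do not mix office readings taken from charts with BpTRU readings in it. That would bring a second measurement method into one wave only.

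The cost is small, because the enrolment readings are already planned: a little more analysis, reliance on a missing-at-random assumption, and possibly a less favourable estimate. The change cannot recover delayed-site patients who left before Time 3, and the report should say so.
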